## Abstract

**Background:**

The increase of allergies is attributed to a multi‐factorial pathogenesis. Multi‐gene traits, as well as different environmental factors, are regarded as responsible for shaping the development of atopic entities. The microbiome's composition in particular seems to play a decisive role in allergy prevention and immunological defense. Another key factor is attributed to the early infant's diet. This trial aims to investigate the influence of an early introduction of processed allergenic foods via premastication, a common practice in human societies throughout the course of human evolution in which the caregiver pre‐chews solids before feeding them to the infant.

**Methods:**

Two parallel study groups of infants at risk for atopic diseases (*N* = 100) are planned to be included. Healthy caregivers of eligible infants can decide to participate by either (A) introducing solids with additional provision of a sugar‐free ground biscuit suitable for pre‐chewing that contains increasing amounts of hen's egg, cow's milk, peanut, and hazelnut proteins or (B) by introducing solids following current feeding recommendations. The primary endpoint will be the assessment of the diversity of the infant's intestinal microbiome. Secondary endpoints will include an assessment of the acceptance of the feeding habit, the development of food allergies or food sensitization, and infections, including potential caries development, in association with the composition of the infant's oral microbiome.

**Conclusion:**

In reflection of the multifactorial pathogenesis of atopic diseases, this trial combines key factors strongly assumed to act “allergy‐protective”: (1) microbial diversity supporting inflammatory resilience and (2) targeted dietary introduction of allergenic foods supporting food tolerance.

**Trial Registration:**

German Clinical Trials Register DRKS00027255. Registered on 29 April 2022.

AbbreviationsAEAdverse EventsAESIAdverse Events of InterestANCOVAAnalysis of CovarianceDBPCFCDouble‐Blind Placebo‐Controlled oral Food ChallengeDMFTDecayed, missing, and filled teethEASI‐ScoreEczema Area and Severity Index ScoreEAT StudyEnquiring About Tolerance StudyeCRFelectronic Case Report FormFASFull Analysis SetGCPGood Clinical PracticeHEAP StudyHen's Egg Allergy Prevention StudyICDAS criteriaInternational Caries Detection and Assessment SystemIgEImmunoglobulin EIgG4Immunoglobulin G4ITTIntention‐To‐TreatLEAP StudyLearning Early About Peanut Allergy StudyPETIT StudyPrevention of Egg Allergy with Tiny Amount Intake StudyPOEMPatient‐oriented Eczema MeasurePPPer ProtocolPPSPer Protocol Population SetREDCapResearch Electronic Data CaptureSAESerious Adverse EventSCORADSeverity Scoring of Atopic DermatitisSPTSkin Prick TestSTAR StudySolids Timing for Allergy Reduction StudyTEWLTransepidermal water loss

Key messagePremastication is a common feeding practice in human societies throughout the course of human evolution in which the mother pre‐chews especially solid foods before giving them to the infant. In this trial, we investigate the infant's microbiome as influenced by different feeding habits. An introduction of weaning food according to current recommendations is compared to an early introduction of processed allergenic foods via premastication.

## INTRODUCTION

1

### Background and rationale

1.1

There have been reports of an increase in food allergies for decades.^1^, ^2^ Currently, up to 10% of children worldwide suffer from IgE‐mediated food allergies^3^ with the most common being allergies to hen's eggs and cow's milk.^4^, ^5^ Additionally, of note are allergies to peanuts and tree nuts due to their association with severe allergic reactions and reduced spontaneous tolerance development.^3^

Allergies are attributed to a multi‐factorial pathogenesis. Multi‐gene traits and diverse environmental factors are regarded as key factors in shaping the development and/or severity of atopic entities.^6^, ^7^, ^8^, ^9^, ^10^, ^11^, ^12^, ^13^, ^14^

#### Microbial diversity supports inflammatory resilience

1.1.1

In continuation of the hygiene hypothesis by Strachan et al.,^6^ various “pro‐allergy” factors have been described over the years, including: reduced household sizes, reduced infections,^7^ higher standards of personal hygiene, Caesarean section delivery,^8^ and limited exposure to pets.^9^ In contrast, a reduced risk of allergic disease development has been attributed to acquisition of hepatitis A/orofaecal microbes via personal contact^10^ or vaginal delivery.^11^ The individual and unique “special environmental experience” has been shown to be reflected in the gut microbiome, especially early in life.^12^ The host acquires mechanisms to distinguish between “microbial friends and foes” on the gut and other mucosal layers.^13^, ^14^, ^15^ A high level of bacterial diversity is suggested to promote the establishment of a tolerogenic immune response towards an inflammatory resilience.^13^

Building on these past findings, we want to analyze if and how the infant's microbiome will be shaped by a traditional infant feeding practice known as premastication.^16^ In this practice, the caregiver pre‐chews food for the infant before feeding it to them and therefore transmits the parental/caregiver oral microbiome.

#### Early dietary intervention in the development of food allergies

1.1.2

The manifestation of food allergies typically begins in early infancy.^3^, ^4^, ^5^, ^17^, ^18^, ^19^, ^20^, ^21^, ^22^, ^23^ The particular focus at this time in life is on the “highly allergenic” foods (like cow's milk, hen's egg, peanut, tree nuts): when they will be introduced (“window of opportunity”), how much they are consumed and how often, or the way they are processed (e.g., raw, heated, hydrolysed). Key studies on this topic include the LEAP trial^22^ (UK), which focused on early peanut introduction, and the EAT study^23^ (UK), which examined the allergy preventive effect of introducing six allergenic foods to breastfed infants starting at 3 months of age. Furthermore, the HEAP (Germany),^18^ STAR (Australia),^19^ and PETIT (Japan)^20^ trials analyzed the introduction of different (and increasing) amounts of hen's egg protein, utilizing either cooked/heated or raw/pasteurized egg protein. A summary of the findings potentially leads to the conclusion that early dietary introduction and the frequent consumption of allergenic foods are regarded as beneficial.^17^, ^21^ Hen's eggs should be introduced thoroughly heated, but not raw.^17^, ^21^

We now want to analyze the parallel introduction of increasing amounts of four “highly allergenic” foods, all processed (baked) in the form of a sugar‐free ground biscuit that is offered to the mother/caregiver for pre‐chewing.

Our aim in using this method is to combine both factors outlined above as they are assumed to act in an “allergy‐protective” manner by: (1) strengthening the microbial diversity that supports inflammatory resilience by transmitting the mother's oral microbiome and (2) targeting dietary introduction of processed allergenic foods that support food tolerance.

We choose an open study design in order to recruit caregivers with a high level of assumed compliance if they choose to take part in the pre‐chewing group.

This is an abridged protocol based on protocol version 2.0 dated 04 October 2021. The approach is prepared in consideration of the Standard Protocol Items: Recommendations for Interventional Trials (SPIRIT) recommendations for interventional trials.^24^

### Objectives

1.2

The primary objective is to compare the impact of different feeding habits on the diversity of the infant's intestinal microbiome. Infants will be introduced to solid food, either with reference to current recommendations as a reference group or by utilizing the traditional feeding practice, by pre‐chewing a sugar‐free ground biscuit in parallel to other weaning foods and breastfeeding (non‐randomized). Secondary objectives focus on the assessment of acceptance of the feeding habit; the development of allergic reactions, including food allergies and food sensitization; and infections, including observation of potential caries development, gastrointestinal problems, and thriving aspects.

### Trial design

1.3

Solids‐by‐Kiss is designed as an exploratory, open, two‐centre trial with two parallel study groups (Group A and B) in infants with risk for atopic diseases (Figure 1).

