#### Intervention description

2.3.1

Mothers of both groups will be encouraged to continue breastfeeding while weaning foods are introduced stepwise to the infant's diet. Parents will decide in advance which group they would like to join, and—depending on the child's individual development—when first complementary foods are to be introduced (Figure 1). All participants will be informed equally regarding current feeding recommendations.^17^, ^21^

All Group A participants will visit the study site at five timepoints (V1–V5). Group B participants will visit the study site at two timepoints (V1 and V5). Blood samples will be collected at V1 and V5; SPT will be performed at V5 only. Samples for microbiome analysis will be taken at indicated visits. Telephone calls are scheduled 2 weeks after V1, V2, V3, and V4 (Group A) and 2 weeks after V1 as well as one interim phone call at week 12 (Group B).

All caregivers will be encouraged to keep a weekly diary recording frequency of pre‐chewing, tolerability, and palatability of solids introduction, as well as any adverse events, concomitant medication, and diet.

V0 (collection of stools + skin swabs) and V6 (enhanced diagnostic in sensitized subjects, including oral food challenges) are optional.

V5 solo consists only of V5 (and optional V6); participants will not have been enrolled before.

Group A – “Interventional/Pre‐chewing Group”: The mother (or one other previously determined caregiver) of an eligible infant will receive a sugar‐free ground biscuit once the infant starts eating complementary foods. The biscuit is ground to ensure homogeneity of the amount of included food proteins. These amounts will be increased by a factor of five in four stages, each lasting 6 weeks ±14 days, V1–V4 (Table 2). The actual amount of total protein of the allergenic food in the first dose at V1 (Table 2) starts slightly below calculated discrete ED05 values for the correspondent food allergens,^25^ which are 2.1 mg peanut protein, 3.5 mg hazelnut protein, 2.3 mg hen's egg protein, and 2.4 mg cow's milk protein. Further ingredients of the biscuit are wheat flour type 550 and margarine processed with rapeseed oil.

**TABLE 2 pai70147-tbl-0002:** Content of Peanut, Hazelnut, Hen's Egg, and Cow's Milk protein in the ground biscuit.

Group A	Visit 1–Visit 2	Visit 2–Visit 3	Visit 3–Visit 4	Visit 4–Visit 5/6

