#### Main secondary endpoints (for further endpoints, please see Appendix S1)

2.4.2

Compliance assessment/adherence of parents/caregivers conducting pre‐chewing via questionnaire on performance and frequency: query on a weekly basis, if performed daily; 4–7 times per week; <3 times/week (compliance defined as at least 4 days/week ≙ 57%)Composition of the oral microbiome and frequency of infant caries by 1 year of age (V5) according to the International Caries Detection and Assessment System (ICDAS, a clinical scoring system allowing detection and assessment of caries lesions and caries experience^30^)Frequency of IgE‐mediated food allergies to at least one of the four foods (hen's egg, cow's milk, peanut, hazelnut) after intervention by 1 year of age (V5) between Groups A and BAllergen‐specific IgE and IgG4 to hen's egg, cow's milk, peanut, hazelnut, Ara h 2, Cor a 14, and wheat at V1 and V5 in comparison between groups.Cumulative occurrence (frequency and severity) of respiratory and gastrointestinal infections (including oral infections) in comparison between groups

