#### Dental examination using telediagnostics

3.1.3

All (pre‐chewing) caregivers will receive a dental examination at V1 using telediagnostics. Caries lesions as well as missing and filled teeth (DMFT Index) will be assessed using the WHO protocol. Caries lesions will be assessed visually according to ICDAS without assessment of ICDAS code 1 (as drying the teeth will not be feasible using tele‐diagnostics).^30^ In case of existing caries lesions, the parent will be asked to treat corresponding lesions before starting the practice of pre‐chewing and will be invited for remaining V1 procedures and initiation of pre‐chewing after dental treatment only. The child's dental chart will be examined at V5 (end of study). Telediagnostics will be provided by an experienced dentist specifically trained upfront.

Please note the Appendix S1 for Continuation of *Clinical Assessment Methods and Clinical Outcome Definitions* on
Skin swabs for microbiome analysisAllergy diagnostic including Skin Prick Test (SPT) and blood samplingDouble‐Blind Placebo‐Controlled Food Challenge (DBPCFC)^35^
Skin Barrier Permeability^36^

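### The trial is called open without limit and no masked reading of infant caries at V5 is described, although the reasons for openness concern only caregivers

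*Protocol article*

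**What the plan says.** Section 1.3 of the protocol article states that the trial "is designed as an exploratory, open". Allocation is by parental choice: "Parents will decide in advance which group they would like to join" (section 2.3.1).

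The reason for openness appears in section 1.1.2: "We choose an open study design in order to recruit caregivers with a high level of assumed compliance". The Discussion adds the worry that too few caregivers will choose pre-chewing, and it acknowledges bias from open selection of the groups. It does not mention bias in reading outcomes.

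The main secondary endpoints (section 2.4.2) include "frequency of infant caries by 1 year of age (V5) according to the International Caries Detection and Assessment System". The Discussion lists the tracking of caries among the ways safety concerns are addressed.

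Section 3.1.3 describes the dental work. On the caregiver side, "caregivers will receive a dental examination at V1 using telediagnostics", with the bracketed qualifier *pre-chewing* placed before the word caregivers. "Caries lesions will be assessed visually according to ICDAS without assessment of ICDAS code 1", because drying is not feasible remotely. A caregiver with lesions is to have them treated before pre-chewing begins. The child's dental chart is examined at V5. On the reader, the section says only: "Telediagnostics will be provided by an experienced dentist specifically trained upfront".

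Table 3 schedules the caregiver's dental status at V1 and the child's at V5 in both groups.

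**The concern.** Openness towards families cannot be avoided here, since a caregiver knows whether she pre-chews. It does not follow that the person scoring the infant's teeth has to know. The article does not separate the two, and its reasons for openness apply only to the first.

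The endpoint leaves room for judgement. ICDAS is a clinical scoring system applied by an examiner, and the question of whether premastication harms or protects teeth is one the Discussion itself treats as contested. A reader who knew the group could be influenced in either direction, so a real harm could be hidden as easily as a false one created. If cases are few, a handful of borderline calls could shape what the trial reports about caries.

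Self-selection into groups is built into this design. Unmasked reading would be a second bias on top of it, and this one could be avoided.

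**Working it through.** The article states no caries rate, power or sample size calculation, so there is no figure of the plan to reproduce. The check has two parts.

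**1. The text set side by side**

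| Question | What the article says | Where |
|---|---|---|
| Is openness limited to certain people? | No | 1.3 |
| Why open? | Caregiver compliance; fear of too few pre-chewing families | 1.1.2, Discussion |
| Is any assessment blinded? | Yes, the optional food challenge at V6 | 2.3.1 |
| Is the V5 caries reading masked? | Not stated | 3.1.3 |
| Does the V5 reader know the group? | Not stated | 3.1.3 |
| Same reader at V1 and V5? | Suggested by the singular dentist, not stated | 3.1.3 |
| Is the V5 child reading remote? | Suggested by the section title, not stated | 3.1.3 |
| Which caregivers are examined at V1? | Text: bracketed pre-chewing qualifier. Tables: both groups | 3.1.3, Tables 3a and 3b |

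The stated reasons do not extend to the outcome reader, and nothing rules out a reader who knows the group. The last row is an inconsistency within the article.

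**2. How much a few calls could matter (illustration)**

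Inputs from the article: 50 infants per group; two-sided 0.05 (section 3.3). All caries and misreading rates below are assumptions.

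*One call.* 1/50 = 2 percentage points.

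*No true cases, k false calls in one group, none in the other.* The two-sided Fisher p is 2 × C(50,k) / C(100,k):

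- k = 5: 2 × 2,118,760 / 75,287,520 = 0.056
- k = 6: 2 × 15,890,700 / 1,192,052,400 = 0.027

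Six of 50 is 12%. If there is one case in the other group, 7 against 1 gives p = 0.059.

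*Equal true prevalence π, with a fraction f of caries-free Group A infants falsely scored as carious.* Expected count in A = 50 × [π + (1 − π)f]; in B = 50π. For π = 0.02 and f = 0.05: 50 × (0.02 + 0.98 × 0.05) = 3.45 against 1.00. Summing the two binomial distributions over all tables with Fisher p ≤ 0.05 gives the chance of a false difference:

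| π | f | Expected A | Expected B | Chance of p ≤ 0.05 |
|---|---|---|---|---|
| 1% | 0 | 0.50 | 0.50 | 0.000 |
| 1% | 2% | 1.49 | 0.50 | 0.002 |
| 1% | 5% | 2.98 | 0.50 | 0.048 |
| 1% | 10% | 5.45 | 0.50 | 0.339 |
| 2% | 0 | 1.00 | 1.00 | 0.000 |
| 2% | 2% | 1.98 | 1.00 | 0.005 |
| 2% | 5% | 3.45 | 1.00 | 0.055 |
| 2% | 10% | 5.90 | 1.00 | 0.300 |
| 5% | 0 | 2.50 | 2.50 | 0.007 |
| 5% | 2% | 3.45 | 2.50 | 0.016 |
| 5% | 5% | 4.88 | 2.50 | 0.058 |
| 5% | 10% | 7.25 | 2.50 | 0.220 |

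The formal test is therefore hard to trip with slight misreading. The expected counts move sooner: at π = 1%, f = 5% makes 0.5 against 0.5 into about 3 against 0.5, and in a small exploratory trial the counts are what readers will look at.

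**The case against.** The strongest objection is that this is an abridged article. Much is referred to Appendix S1, which is not available here, and reader masking may be set out there or in the full protocol. That stands as far as it goes: the omission alone is not an error. However, the assessment topics that section 3.1.3 passes to the appendix are skin swabs, allergy diagnostics, the food challenge and skin barrier, not the dental reading. The point also rests on what the article does state, namely an unlimited open design with reasons that cover only caregivers.

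Several stronger readings are tempting and are not supported:

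- *The dentist reads infant caries knowing the group.* The article does not say so; it only leaves it possible.
- *Examining caregivers at V1 tells the dentist who pre-chews.* Table 3b schedules the same check in Group B, so the examination alone does not reveal the group. The rule on treating lesions before pre-chewing links the dental result to Group A, but only for caregivers with lesions.
- *Infants' teeth are scored undried.* The sentence on drying and ICDAS code 1 belongs to the caregiver examination.
- *The authors expect caries to go one way.* The Discussion reports opposing views, so no direction of bias can be assumed.
- *Laboratory samples need coded labels for the same reason.* The article describes no problem there.

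It is also fair to say that the endpoint is secondary, that section 3.3 treats such analyses as explorative, and that self-selection is the larger, acknowledged bias. This limits the weight of the point. It is no reason to leave an avoidable bias in place.

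**Conclusion.** The point holds as a design gap of modest weight. An unqualified open design, justified only by caregiver recruitment and compliance, leaves the V5 reading of infant caries open to knowledge of the group, and section 3.1.3 describes nothing to prevent it. Whether the reader would in fact know the group cannot be settled from the article.

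The size cannot be derived from the article either. Under assumed true rates of 1% to 5%, one-sided over-reading of 2% gives a false significant difference in under 2% of trials, of 5% in about 5 to 6%, and of 10% in 22 to 34%, against under 1% with no over-reading. These figures assume that all misreading falls in one group. They show that a few calls could shape the caries comparison, not that they will.

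Separately, section 3.1.3 and Table 3b do not clearly agree on whether Group B caregivers have a dental examination at V1.

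**What to change.** 1. In section 1.3, say that the trial is open for families and for the staff who supervise feeding.
2. In section 3.1.3, say that the V5 infant dental records or images are read under a code, without the group and without the caregiver's V1 chart. State who reads them and whether the reading is live or from a record. If Appendix S1 already sets out a masked reading, a cross-reference is enough.
3. Reconcile the bracketed pre-chewing qualifier in section 3.1.3 with the Group B entry in Table 3b.

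The cost is protocol wording and coded labels on the V5 dental material. Recruitment, the intervention, the sample size and staffing are unchanged. The small downside is that, if the reading is live, a family may occasionally reveal its group; noting when this happens would be sufficient.

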**FIGURE 1 pai70147-fig-0001:**
[figure not shown]
The sugar‐free ground biscuit* contains defined amounts of hen's egg, cow's milk, peanut, and hazelnut proteins, which will be increased from levels around ED05 in four steps by a factor of five at each step. In Group A, the first (pre‐chewed) portion will be given under medical supervision at the study site (V1, 4–8 months of age) followed by feeding at home once daily. At V2: 6 weeks after V1 ± 14 days, infants will receive the new ground biscuit, with protein from each of the four food allergens increased by a factor of five; the same will happen at V3 (6 weeks after V2 ± 14 days) and V4 (6 weeks after V3 ± 14 days). The first portion of each ground biscuit with increased protein content will be given at the study site under direct, two‐hour medical observation. * The ground biscuit will be analyzed on microbiological criteria for foodstuffs in accordance with COMMISSION REGULATION (EC) No. 2073/2005. d, days; DBPCFC, double blind placebo controlled food challenge; h, hours; wk, weeks.

The trial is part of the collaborative project Solids‐by‐Kiss (Please see “Funding”). Subprojects address (1) development and production of the “test‐biscuit”; (2) its qualitative and quantitative analytical verification; (3) consumer communication including allergen‐labelling; and (4) diagnostic methods for microbiome analysis. Subprojects will be described separately.

## METHODS: PARTICIPANTS, INTERVENTIONS, AND OUTCOMES

2

### Study setting

2.1

All visits throughout the study will take place either in the study centres (V1–V5) or on the ward (V0: on the ward of the Division Obstetrics and Prenatal Medicine, Goethe University Frankfurt, Frankfurt am Main, Germany, and V6: on the ward of the Department of Pediatrics, Division of Pneumology, Allergology, Infectious Diseases and Gastroenterology, Goethe University Frankfurt, or of the Department of Pediatric Respiratory Medicine, Immunology and Critical Care Medicine, Charité – Universitätsmedizin Berlin).

### Eligibility criteria

2.2

Only healthy participants can take part in the study. The detailed inclusion and exclusion criteria are listed in Table 1.

**TABLE 1 pai70147-tbl-0001:** Inclusion and exclusion criteria for Group A or Group B.

Inclusion criteria	Exclusion criteria
For the infant	For the infant
Healthy, full‐term born infants Positive family history for atopic diseases (at least one parent or sibling suffers from atopic diseases such as atopic eczema, food allergy, allergic rhino conjunctivitis, allergic asthma)	Previously consumed hen's egg, peanut, or hazelnut^a^ Suffering from a medically diagnosed wheat allergy
For the caregiver	For the caregiver
No food allergies to hen's egg, cow's milk, peanut, wheat, or hazelnut No (acute, sub‐chronic, or chronic) infectious diseases (including caries) according to physician's decision Mental and linguistic capability to follow the protocol requirements	Any reported disease or medical condition (for example, but not limited to, severe concurrent disease, infection, open wounds in the mouth, comorbidity, for example, acute trauma, serious oncological disease, serious renal disease, relevant cardiovascular disease, autoimmune diseases) or reasons that may, in the opinion of the study physician, interfere with the ability to participate in the study, cause undue risk, or complicate the interpretation of data concerning child or caregiver

^a^
Previous consumption of cow's milk, for example, as infant formula, is allowed since infant formula is commonly produced using cow's milk and formula‐fed infants should not be excluded.

Please see Appensix S1 for further information.

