Group B – Non‐randomized reference: Solids will be introduced with reference to current feeding recommendations^17^, ^21^ based on the parents' decision but without pre‐chewing. Study participants will be invited for the end of study visit (V5) around the child's first birthday.

V5 solo consists only of V5 in Group B (and optional V6); participants will not have been enrolled before. This group serves as an additional reference group, as participants will not have been informed (biased) about premastication before.

At V1 and V5, blood samples from the infant will be collected and stored for allergy diagnostics (including food‐specific IgE and IgG4 to hen's egg, cow's milk, peanut, hazelnut, Ara h 2, Cor a 14, and wheat).

At V5 (or V5 solo), infants will be skin prick tested with hen's egg, cow's milk, hazelnut, and peanut.

In case of the detection of a food‐specific sensitization (elevated food‐specific IgE (>0.1 kU/L) or positive Skin Prick Test, SPT (wheel size >3 mm)) at V5, a double‐blind, placebo‐controlled oral food challenge (DBPCFC) will be offered for evaluation of clinical relevance (optional visit V6). Consequently, parents will be advised to continue feeding the study product until the DBPCFC is performed.

Importantly, apart from the intervention with the ground biscuit in group A, there are no further dietary restrictions imposed by the study protocol for both of the study groups.

All participants may continue their usual medications, as well as those taken for any concomitant diseases, including wheezing and eczema, throughout the study. All subjects who will undergo a DBPCFC will be advised to discontinue oral antihistamines 3–5 days before their appointment. For a detailed description of all study procedures, see Table 3.

**TABLE 3 pai70147-tbl-0003:** Schedule of Events: (a) Group A and (b) Group B.

Visit/Phone call	Enrolment/Screening		Intervention period							V5	(V6)^a^	Unscheduled visit^b^
	V0 (optional)	V1	PC 1	V2	PC2	V3	PC3	V4	PC4			
(a) *Schedule of Events – Group A*												
Timepoint (week)		0	2 wks after V1	6 wks (±14 d)	2 wks after V2	12 wks (±14 d)	2 wks after V3	18 wks (±14 d)	2 wks after V4	24 wks (±14d)		
Enrolment												
Informed consent	x	X^e^										
Check eligibility	x	X^e^										
Assessments												
Demographics/subject characteristics	x	x								x		
Family characteristics	x	x		x		x		x		x		
Medication, nutrition, exposure to smoking during pregnancy	x	x										

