### Harms

4.1

Any adverse event (AE) will be documented on paper (diary). Adverse events of special interest (AESIs) as well as serious adverse events (SAEs) will also be documented in the Research Electronic Data Capture, REDCap (Vanderbilt University in Nashville, USA). In case of an AESI, caregivers will be strictly advised to contact the study site as soon as possible. SAEs have to be reported within 48 h after knowledge of the event to the principal investigator. An SAE will be defined as any AE that fulfills at least one of the following criteria: results in death; is life‐threatening; requires inpatient hospitalization (longer than 24 h) or prolongation of existing hospitalization; or results in persistent or significant disability or incapacity.

The following are considered as AESIs:
Objective immediate‐type allergic reactions within 2 hours of food exposure (either to the study product or due to exposure to other food allergens). Caregivers will be asked to call for medical help (emergency call), to document the symptoms in the subject's diary, and to call the study site before giving the next dose of the study product (Group A) in order to assess further details.Recurrent gastrointestinal symptoms/abdominal pain. Caregivers will be asked to document the symptoms in the subject's diary and to call the investigational site.Any form of new onset eczema should be reported immediately. An unscheduled site visit for visual examination and diagnosis of atopic dermatitis using modified Hanifin and Rajka criteria will be carried out according to investigators' discretion.^31^, ^32^, ^33^, ^34^ In case of a pre‐existing (at screening) or newly diagnosed atopic dermatitis, caregivers will be handed out an extra diary.

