## DISCUSSION

5

In Solids‐by‐Kiss, we have designed a sugar‐free ground biscuit that contains increasing amounts of foods considered to be “highly allergenic”: hen's egg, cow's milk, peanut, and hazelnut. The biscuit is offered for pre‐chewing.

We are not aware of any prospective trials, especially not in the allergy area, analyzing the effect of pre‐chewing on the infant's microbial profile.^16^ Research on benefits or risks of premastication appears to be scarce and is mainly based on observations and case reports.^16^ Nevertheless, next to potential beneficial aspects, the transmission of pathogenic germs requires very careful consideration. As an example, for a long time the oral transfer of caries—regarded as an infectious disease induced by special bacteria like *Streptococcus mutans*—was recommended to be strictly avoided.^40^ In contrast, recent hypotheses support the development of a diverse, balanced oral microbiome for caries prevention.^41^, ^42^, ^43^, ^44^

It is important that the transmission of any diseases is reported, particularly when the person who pre‐chews the food is ill themselves. Just recently a case of HIV transmission by an HIV‐infected caregiver has been published.^45^

For this first exploratory approach, only healthy, full‐term born infants and healthy caregivers will be eligible for inclusion. Safety concerns are addressed as thoroughly as possible through constant referral to the precautionary measures in the instructions for administering the study product and close monitoring of infections or of any adverse reactions in the caregiver or the child. We track caries by examining the dental status of the caregiver and later of the infant and analyzing their oral microbiome pre and post intervention.

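### The eligibility section admits only healthy infants, but the harms section provides for atopic dermatitis already present at screening, and the protocol does not say how the two fit together

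*Protocol article*

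**What the plan says.** Section 2.2 opens its criteria with "Only healthy participants can take part in the study". Table 1 lists "Healthy, full‐term born infants" as an inclusion criterion, together with a family history of atopy. The infant exclusions are earlier consumption of hen's egg, peanut or hazelnut, and "Suffering from a medically diagnosed wheat allergy". Eczema, atopic dermatitis and wheeze are not named. The Discussion restates the restriction when it introduces the safety precautions: only healthy, term "infants and healthy caregivers will be eligible for inclusion".

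Section 4.1 (Harms) covers new-onset eczema as an event of special interest and then adds: "In case of a pre‐existing (at screening) or newly diagnosed atopic dermatitis, caregivers will be handed out an extra diary".

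Section 2.3.1 states: "All participants may continue their usual medications, as well as those taken for any concomitant diseases, including wheezing and eczema, throughout the study". Table 3 schedules SCORAD, EASI and POEM at V1. Section 3.3 names analysis of covariance for continuous secondary endpoints and gives SCORAD as an example. The covariates it names are sex, birth mode, siblings and pets, followed by an unspecified remainder.

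**The concern.** An entry criterion has to give the same answer for the same infant at both sites. Here one section appears to turn away an infant with atopic dermatitis at screening, and another tells staff what to hand that infant's caregiver. Nothing in the text shown ranks one statement above the other.

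Two things are at stake. First, the description of the sample: if the Harms section is followed, the Discussion's account of who was eligible is not accurate for part of the sample. Second, comparability: parents choose the group, so no randomisation balances eczema at entry between Group A and Group B. SCORAD is itself an analysed endpoint, and its baseline value bears directly on its value at V5.

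**Working it through.** The protocol gives no figure to reproduce on this point, so the check sets the statements side by side.

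1. **General rule.** Section 2.2, Table 1 and the Discussion all require healthy infants. None of them says what healthy excludes.
2. **Specific exclusions.** Table 1 names three foods already eaten and wheat allergy. It neither excludes nor permits eczema. A catch-all in the caregiver column lets the study physician exclude for reasons affecting interpretation of the child's data. That is a site-level judgement and does not settle the matter.
3. **Harms section.** The provision covers "In case of a pre‐existing (at screening) or newly diagnosed atopic dermatitis". The bracketed words rule out the reading that only disease arising after entry is meant. Handing out a diary presupposes enrolment.
4. **Concomitant medication.** The reference to "those taken for any concomitant diseases, including wheezing and eczema, throughout the study" fits eczema present at entry, but also eczema that begins later. It is supporting evidence only.
5. **Scores at V1.** A baseline SCORAD or EASI may be zero, so scheduling these scores is consistent with either entry rule.
6. **When eligibility is judged.** Table 3 marks the eligibility check at V0 and V1, and its footnote requires the V1 check only if it was not done at V0. V0 is optional and is located on the Frankfurt obstetrics ward (section 2.1). V1 takes place at 4 to 8 months (Figure 1 legend). An infant checked at V0 need not be formally rechecked at V1, whereas an infant without V0 is first judged at 4 to 8 months. An undefined criterion is thus applied at different ages, and the difference partly follows centre.

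**Worked case.** Take an infant seen first at V1, aged 5 months, with eczema. On a literal reading of section 2.2 the infant is not healthy and is not enrolled. Under section 4.1 the infant is enrolled and the caregiver receives the extra diary. The same infant checked at V0, before any eczema appeared, would already have passed.

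**Illustrative size (assumption).** The documents give no prevalence of atopic dermatitis at entry. With 50 infants planned per group:
- at 10%: 0.10 × 50 = 5 infants per group;
- at 25%: 0.25 × 50 = 12.5, so about 12 infants per group.

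**Cost of adjustment.** Assume all 100 infants have V1 and V5 scores and each named covariate enters as one term. The model then has 6 parameters (intercept, group, sex, birth mode, siblings, pets), leaving 100 − 6 = 94 residual degrees of freedom. Adding V1 SCORAD leaves 93.

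**The case against.** The best defence is that healthy means generally healthy. Table 1 lists wheat allergy separately, which would be redundant if the word already barred every atopic condition. Read with the medication and harms provisions, the intended rule may be that eczema is admissible and monitored. The article is also abridged and refers to Appendix S1 for more on eligibility, where a definition may stand. This has force: the intent may be clear to the investigators. It does not remove the conflict, because the published text makes statements that pull in opposite directions and would need aligning whatever the appendix says.

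Several stronger inferences are tempting, and the documents do not support them:

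- A reader might infer that infants with eczema carry the highest allergy risk, or would supply most food-allergy events. The protocol defines risk by family history and does not rank infants by eczema.
- A reader might use the Introduction's worldwide figure of up to 10% for food allergy to cap the expected events. That figure describes children in general and is no upper bound for infants selected for family history.
- A reader might infer that eczema is left out of the adjustment. The covariate list is open-ended, so eczema is unnamed rather than excluded, and a fuller list may sit in the analysis plan.

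The defence can also fairly say that the trial is exploratory, that its primary endpoint is gut microbiome diversity, and that the Discussion already concedes self-selection bias and disclaims allergy-prevention recommendations. Clearer entry wording would not remove that self-selection. These points limit the severity.

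**Conclusion.** The inconsistency is real and minor. Section 2.2 and the Discussion restrict entry to healthy infants, while section 4.1 assumes that some enrolled infants have atopic dermatitis at screening. With the term undefined in the text shown and the check made at V0 or V1, the two centres may decide differently. The document does not show that they have done so.

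The statistical consequence is narrow. It concerns mainly the SCORAD comparison between self-selected groups, and it arises only if such infants are enrolled. The number affected is unknown; the illustrative 5 to about 12 per group depends entirely on the assumed 10 to 25%. The conclusion also assumes that Appendix S1, which is not shown, does not already reconcile the passages. This review takes no position on which entry rule is right.

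**What to change.** **Reconcile the text.** Align section 2.2, Table 1, section 4.1 and the Discussion, and check the medication sentence in section 2.3.1 against the result. State in Table 1 whether atopic dermatitis at entry is compatible with being healthy, and whether this is judged at V0 or V1.

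**If such infants are enrolled:**
- Name V1 SCORAD as a covariate in the analysis of covariance of SCORAD at V5, for Group A and Group B infants enrolled at V1. V5-solo infants have no V1 value and cannot enter this model.
- Use it in the food-allergy and sensitisation models only as far as the number of events allows, since sparse logistic models may not support another term.
- Report eczema at V1 by group and centre.

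**Cost.** A line in Table 1, matching wording elsewhere, one degree of freedom and one descriptive table. No new data are needed for infants enrolled at V1, because the score is already scheduled there.
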